#### Management and Governance

The process evaluation is to be conducted in parallel with the MIMeRiC trial; some data will be collected together for the two studies. Data analysis for the two studies will also be conducted in parallel. The same researchers are responsible for the RCT, delivering the intervention, and planning and conducting the process evaluation; our small research team and restrictive funding did not allow for any independent evaluators to be involved [3].

Most of the research questions are covered by the ethical approval obtained for the RCT, but a supplemental ethical approval was granted for qualitative study of the patients’ experience of the intervention (interviews) and their views on the follow-up care after discharge (questionnaire).

## Methods

### Overall Study Design

The process evaluation is a mixed-method study. Three research questions will be studied using qualitative methods, three using quantitative methods, and one using a mix of qualitative and quantitative methods. This was based on the MRC guidelines: “Hence, when feasible it is often useful to combine quantitative data on key process variables from all sites or participants with in-depth qualitative data from samples purposively selected along dimensions expected to influence the functioning of the intervention” [3].

### Methods for Research Question 1: What Was Actually Delivered in the Medication Review?

This will be studied using a descriptive, quantitative method. The number and type of DRPs will be described using the 7 categories suggested by Cipolle and colleagues: (1) adverse drug reaction, (2) ineffective drug, (3) need for additional drug therapy, (4) dosage too low, (5) dosage too high, (6) unnecessary drug therapy, and (7) noncompliance. If acting on the DRPs has any effects that are documented in the electronic health record (EHR), these will also be described. Data are collected from the pharmacists’ documentation in the EHR and from separate study notes about DRPs that pharmacists record during the intervention. Data on the effects of actions on DRPs will be collected from the EHR; the pharmacists’ documentation will be used with laboratory results, documentation by primary care or other professionals at the cardiology clinic when relevant.

### Methods for Research Question 2: How Did the Cardiologists Experience the Involvement of and Interaction With a Clinical Pharmacist?

This question will be answered by a qualitative questionnaire to cardiologists with 4 questions: (1) What is your opinion about the patients having a consultation with a pharmacist to discuss their medicine regimen, after the standard follow-up with a physician? (2) What is your opinion about the pharmacists conducting a medication review and contacting you as a cardiologist to consider their suggestions? (3) What is your opinion about the collaboration with the pharmacists in the study? (4) Would you like to add anything else?

Questionnaires will be issued at the end of the intervention period and answered anonymously by the cardiologists. Collected data will be analyzed with inductive content analysis.

### Methods for Research Question 3: Was the MI Used Consistently With MI Principles?

This will be a quantitative assessment of the integrity of MI delivered by the clinical pharmacists. All in-person consultations in the intervention group are audio-recorded if permitted by the patient. A random sample of these recordings, the number corresponding to 20% of in-person consultations, will be coded with the Motivational Interviewing Treatment Integrity behavioral coding system version 4.2.1 (MITI 4.2.1) [44] by an independent coding institute (the MIQA group at the Karolinska Institute, Stockholm). A randomly selected 20 min of these recordings will be coded; for one-third of the consultations, the first 20 min will be coded; for one-third, the middle 20 min will be coded; and for one-third, the last 20 min will be coded. Competency in MI will be described by four global scores: cultivating change talk, softening sustain talk, partnership, and empathy. In addition, the ratios of change talk to sustain talk and questions to reflections will be assessed. These scores and ratios will be related to recommended levels of MI competency. The target behavior of the MI consultations is defined as: start taking medicines regularly or maintain this behavior. Changing a patient’s attitude toward their medicines in a positive direction is a strategy for maintaining or reaching the target behavior of regularly taking the medicines. On the basis of our theoretical framework and our pilot evaluation, we assumed that patients with a negative attitude need the MI component of the intervention, and should have this, whereas accepting patients are considered adherent and the need for MI might be less obvious. These patients are targeted by the intervention partly to maintain their target behavior but primarily to solve other DRPs and to improve the quality of prescribing. However, there is no distinct line between these groups; problems with adherence can arise in the group with an accepting attitude as well. To ensure that both groups are equally represented in the assessment of consultations, we will stratify the samples so that 20% of consultations with patients with a negative attitude and 20% of consultations with patients with an accepting attitude are coded. For the latter group, it might be that DRPs make the target behavior undesirable for a particular drug and, if so, only two of the global scores—partnership and empathy—will be used. Such consultations without a target behavior will be valued on a scale for person-centeredness instead of MI competency. The analysis will inform about the frequency of consultations with a target behavior (among the random sample), the fidelity of MI, and the fidelity of person-centered consultations.

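### RQ3 benchmarks the ratio of change talk to sustain talk as pharmacist MI competency, although that ratio is patient speech and reflects the patient's starting position as well as the pharmacist's skill

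*Protocol article*

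**What the plan says.** All of this stands in the Protocol article, mainly in the section on methods for Research Question 3.

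- Purpose: "This will be a quantitative assessment of the integrity of MI delivered by the clinical pharmacists".
- Main measures: "Competency in MI will be described by four global scores: cultivating change talk, softening sustain talk, partnership, and empathy".
- Additional measures, and the use made of all of them: "In addition, the ratios of change talk to sustain talk and questions to reflections will be assessed. These scores and ratios will be related to" [competency benchmarks for MI].
- What the talk is about: "The target behavior of the MI consultations is defined as: start taking medicines regularly or maintain this behavior".
- The two patient groups: those with a negative attitude are assumed to need the MI component, "whereas accepting patients are considered adherent and the need for MI might be less obvious". The section adds that the line between the groups is not sharp and that accepting patients can also develop adherence problems.
- Sampling: 20% of consultations are coded within each attitude group.
- Exception: where drug-related problems leave a consultation without a target behavior, only partnership and empathy are scored. The consultation is then rated on person-centeredness, not on MI competency.

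The Results section reports 64 consultations coded and not yet analyzed.

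**The concern.** RQ3 concerns the provider. The four global scores and the question-to-reflection ratio describe what the pharmacist does. The ratio of change talk to sustain talk describes what the patient says for and against taking medicines regularly. The article does not define the terms, but its own list of skills makes the reading clear: the pharmacist cultivates one kind of talk and softens the other, so the talk is the patient's. The pharmacist's contribution is already covered by those two global scores.

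The process evaluation is meant to explain why the intervention worked or did not. For that, MI that was poorly delivered has to be told apart from MI that was well delivered to patients who did not respond. Comparing a patient-response measure with a competency level blurs that distinction for this measure. A favorable ratio may partly show that many coded patients already favored taking their medicines. An unfavorable one may partly show that many were reluctant, which is the group in which MI is chiefly meant to act.

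**Working it through.** The article states no value, threshold or sample-size figure for the talk ratio, so there is nothing to reproduce. The check has two parts.

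**1. Whose behavior each measure describes**

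| Measure | Describes | Related to competency levels? |
|---|---|---|
| Four global scores | Pharmacist | Yes |
| Questions to reflections | Pharmacist | Yes |
| Change talk to sustain talk | Patient, in response to the pharmacist | Yes |

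Only the last row does not fit a purpose defined as the integrity of what pharmacists delivered.

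**2. How far a pooled ratio could move with skill held constant**

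Inputs:
- s, the share of coded consultations that are with negative-attitude patients. The documents do not give it. The pilot found 10 of 21 patients with a potentially unfavorable attitude (10/21 = 0.476). That is a share of patients, whereas the coded unit is the consultation. Patients have 2 to 5 meetings depending on need, and the pilot led to a decision to intensify or prolong the intervention for negative-attitude patients, so their share of consultations may be higher. Range used: 0.20 to 0.80.
- c_acc and c_neg, the change-talk share of patient talk in accepting and negative-attitude patients. These are assumptions; the documents give no figures.
- Each consultation is assumed to contribute the same amount of talk.

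Formulas: pooled share p = s × c_neg + (1 − s) × c_acc; pooled ratio = p / (1 − p).

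Worked case at the pilot share with c_acc = 0.75 and c_neg = 0.50: p = 0.476 × 0.50 + 0.524 × 0.75 = 0.631, and the ratio is 0.631 / 0.369 = 1.71.

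| c_acc | c_neg | Stratum ratios (accepting; negative) | s = 0.20 | s = 0.476 | s = 0.80 |
|---|---|---|---|---|---|
| 0.50 | 0.50 | 1.00; 1.00 | 1.00 | 1.00 | 1.00 |
| 0.60 | 0.50 | 1.50; 1.00 | 1.38 | 1.23 | 1.08 |
| 0.75 | 0.50 | 3.00; 1.00 | 2.33 | 1.71 | 1.22 |
| 0.75 | 0.40 | 3.00; 0.67 | 2.13 | 1.40 | 0.89 |

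The first row shows the condition: if the groups talk alike, mix has no effect. The other rows show that if they differ, the ratio moves although skill does not. The table does not estimate the size in this trial, because the stratum ratios simply restate the assumed shares.

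The sampling rule does not change this. Taking the same fraction, 20%, from each group reproduces the consultation mix in the coded sample. It does make reporting by group possible.

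**The case against.** The strongest case against the point has five parts.

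- **Patient talk is partly the pharmacist's product.** The article's introduction to MI names evoking the client's own motivation as one of its core processes. This stands: the ratio carries some information on delivery and is not a pure measure of case mix.
- **Dependence on attitude is not documented.** This also stands. The article gives no talk data and says the groups overlap. A difference in talk is a plausible inference from describing one group as adherent and the other as needing MI, and no more than that.
- **No pooling is stated, and tabulation may be left to a fuller document.** Correct, so the absence of stratum tables is not the fault raised here. The point is the stated rule that relates the ratio to competency levels.
- **Consultations without a target behavior leave the MI competency scoring.** This removes some consultations for which the ratio would make little sense. Accepting patients who do have a target behavior remain.
- **The ratio is only an addition.** True, and it limits the harm.

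A reader might go further and infer that RQ3 cannot tell whether a null effect on adherence came from poor MI delivery. The documents do not support that. Competency is described mainly by the four global scores, which with the question-to-reflection ratio still inform on delivery, and no composite or pass/fail rule lets the talk ratio override them.

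**Conclusion.** The point holds in limited form. A measure of patient speech is compared with a standard for provider skill, in a section whose declared object is what the pharmacists delivered. That rests on the article's wording alone. That the ratio also shifts with the mix of attitudes rests on an assumption about patient talk which the documents neither state nor quantify. Under the assumed values, the pooled ratio at constant skill ranges from no movement at all to between 2.33 and 1.22, or between 2.13 and 0.89, over negative-attitude shares of 20% to 80%.

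The consequence is confined to one supplementary, descriptive measure in the process evaluation. It does not touch the outcomes of the randomized trial. It is worth correcting because the correction is cheap and the coded data had not been analyzed when the article was written.

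**What to change.** Amend the wording for RQ3 as follows:

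1. Do not compare the change-talk to sustain-talk ratio with recommended competency levels. Base the competency judgment on the four global scores and the question-to-reflection ratio.
2. Keep the talk ratio, but label and report it as a measure of patient response.
3. Report the talk ratio and the fidelity scores for the negative-attitude and accepting strata already used for sampling, alongside the overall result. Neither stratum should become the main result, since the authors want both groups represented.

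No new data or coding are needed. The cost is precision. If the 64 coded consultations split as the pilot patients did, there would be about 64 × 10/21 = 30.5 negative-attitude and 64 × 11/21 = 33.5 accepting consultations, before removing any without a target behavior. With equal variance and independent consultations, standard errors would be about √(64/30.5) = 1.45 and √(64/33.5) = 1.38 times that of the overall figure. The change should be recorded before the coded results are examined.

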
### Methods for Research Question 4: Did the Intervention Change How the Patients Felt, Reasoned About, or Acted Toward Their Cardiovascular Medicines?

This will be studied qualitatively by assessing how patients’ experiences of the intervention relate to the intended mechanisms of the intervention, as described in the conceptual model (Multimedia Appendix 2) and the framework for the process evaluation. For this question, the method of focus group interviews was chosen because it is an effective method of gathering information and is especially valuable in the evaluation of program experiences. The main advantage of focus groups over individual interviews is the richness and quality of the data that arise, because participants are listening to the answers of others. Comments might trigger memories and thoughts that would not come up in individual interviews, and participants’ comments on each other weed out false or extreme views [45].

Three focus group interviews will be carried out with 4 to 6 intervention patients in each group. The interview and discussion will be led by a moderator, a pharmacist who is familiar with the study but is not involved in the care of the patients. Because the intervention is primarily intended to affect beliefs and adherence among those who have a negative attitude and therefore a higher risk of nonadherence, the sample of patients chosen for the focus groups will be from patients with a negative attitude toward their medicines at baseline. With purposeful sampling among the patients who have taken part in the full intervention, we will try to cover both men and women, those newly diseased and those with a history of CHD, those with acute and those with chronic disease, and those who changed their attitude after the intervention in addition to those who did not.

Questions will be asked about how the patients experienced the consultation with the pharmacist and how they perceived that it had affected their medicine-taking behavior or their reasoning about medicines. The moderator will encourage the patients to describe all aspects by using probing questions. The moderator will also be supported by an observer whose main role will be to record all nonverbal communication in the focus groups. The focus group interviews will be audio-recorded and transcribed verbatim and then analyzed using deductive content analysis. A coding scheme of categories will be constructed based on the conceptual model about how the intervention is intended to work on adherence. The moderator will not be analyzing the interviews but will be accessible for questions about how to read the transcripts.

### Methods for Research Question 5: Did the Intervention Change the Patients’ Beliefs About Their Cardiovascular Medicines?

This will be studied primarily quantitatively, but certain aspects will also be illustrated qualitatively by the interviews with patients.

Data on beliefs about medicines will be collected in the MIMeRiC trial with the BMQ-S instrument administered 3 times: baseline (after the standard care follow-up), after 10 months (during the intervention), and after 15 months (after the intervention). In this study, we will ask the patients to consider only their heart medicines as they answer the BMQ-S. The instrument consists of two subscales, one for the perceived necessity for the drugs and one for perceived concerns about the drugs. The two subscales have 5 items each and are assessed by a 5-point verbal descriptor scale ranging from strongly disagree to strongly agree.

As instructed by the originators, numerals (1-5) will then be assigned to each statement of agreement to summarize each subscale with 5 to 25 points. The difference between the necessity and concern scales (range: −20 to 20) will then be related to the cost-benefit analysis for each patient’s medications. A positive difference means that the patient perceives the benefit of taking the drugs to outweigh the risks of taking the drugs, and the more positive the difference is, the more adherent the patient is supposed to be [9]. It has also been found that categorization based on high (>15) or low (<15) scores on each scale, yielding 4 categories (accepting, ambivalent, neutral, and skeptical) predicts adherence behavior [46,47]. Because the scales have ordered verbal categories, it is not correct to assign numerals and sum them to a global score, because the data are only ordered within the structure while the distance between the agreement statements or the magnitude of them is not known [48]. Even though the categorization also depends on the global sum of each scale, this is a more correct way of handling the data. Therefore, we chose this as our primary outcome in analyzing the effects of the intervention on beliefs. The stratified randomization of patients in the MIMeRiC trial was also based on these four categories.

In this study, we will:

analyze whether there is a difference between the control group and the intervention group in the proportion of patients in each category at follow-up (15 months)describe temporal changes in the 4 categories over the 3 assessments in the control and the intervention groupsanalyze changes in the sum of each subscale, and differences between the intervention and control groupsanalyze changes in each item of the scales, and differences between the intervention and control groupsanalyze the transcribed material from the focus group interviews with intervention patients described above using deductive content analysis methods, based on the 10 items of BMQ-S, as a way of including the results of the quantitative study of beliefs

While item 1 in the list is a primary objective, items 2 to 5 refer to secondary objectives.

Analyses 1 to 3 will be adjusted for variables thought to be influential: sex, age, type of CHD, and history of CHD. In our pilot study, most patients with an ambivalent attitude toward their drugs had a history of CHD [42].

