#### Conceptual Model of Change

On the basis of the adherence model by the WHO, the RAA as a more general model for predicting behavior, and our understanding of how prescribing treatment determines outcomes, we made a conceptual model of how the change processes of the intervention would act to change the outcomes we set out in our RCT [6]. The model in Multimedia Appendix 1 describes how the optimized outcomes follow from full adherence to the optimal treatment, and how the intervention acts by two methods to improve these variables. MI is thought to act on the adherence variable and the medication review on the treatment variable. The intervention can only affect the outcomes if a patient has a problem with adherence (current or expected in the future) and/or treatment quality.

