#### Study Design of the RCT in Brief

The MIMeRiC trial is an RCT with 2 parallel groups (N=418) and 12 months follow-up. Patients with CHD identified and followed at the cardiology clinic of Kalmar County Hospital are randomized to usual care (control) or usual care plus a follow-up program with medication review and MI. Ethical approval has been obtained from the Regional Ethics Committee, Linköping (Dnr-2013/236-31). The trial (clinicaltrials.gov, NCT02102503) has been fully described in the forthcoming protocol [6]. Patients in the intervention group meet a clinical pharmacist at the cardiology clinic 2 to 5 times during the year after discharge depending on need, and problems with adherence or prescribing are solved in collaboration with the patient and/or the cardiologist.

The primary outcome of the trial is the proportion of patients reaching the treatment goal for low-density lipoprotein cholesterol. Secondary outcomes involve the effects on blood pressure, patient adherence, quality of life, and health care use. An economic evaluation of the intervention is also planned.

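### The beliefs analysis compares whole arms only and omits baseline attitude from its covariates, although belief change is aimed mainly at patients with a negative baseline attitude

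*Protocol article*

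**What the plan says.** Under Methods for Research Question 5, the protocol article lists five analyses. Item 1 looks for a "difference between the control group and the intervention group in the proportion of patients in each category at follow-up (15 months". Item 2 describes category changes over the three assessments by arm. Items 3 and 4 compare subscale sums and single items between arms. Item 5 is a qualitative reading of focus groups held with intervention patients only. The ranking is explicit: "While item 1 in the list is a primary objective, items 2 to 5 refer to secondary objectives". So are the covariates: "Analyses 1 to 3 will be adjusted for variables thought to be influential: sex, age, type of CHD, and history of CHD".

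Other sections give baseline attitude a central part:

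- Methods for Research Question 4 restricts the focus groups to negative-attitude patients because "the intervention is primarily intended to affect beliefs and adherence among those who have a negative attitude".
- Methods for Research Question 3 samples recordings by attitude. It says accepting patients are included partly to sustain their medicine-taking, but chiefly for drug-related problems and prescribing quality.
- The pilot evaluation reports that 10 of 21 patients had a potentially unfavourable attitude and that a need to stratify on baseline beliefs was seen.
- Methods for Research Question 5 confirms this was done: "The stratified randomization of patients in the MIMeRiC trial was also based on these four categories".

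**The concern.** The article states in advance that the effect on beliefs should depend mainly on where a patient starts. It uses baseline attitude to randomise, to sample recordings and to choose focus group members, but not in the randomised comparison of beliefs. There it is neither a covariate nor a factor by which the effect is estimated.

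The stated aim of the process evaluation is to understand how and why the intervention did or did not work. If the whole-arm difference is small, the listed quantitative analyses do not show whether negative attitudes failed to shift, or shifted in a subgroup and were averaged with patients who had less room to move. Leaving the stratification factor out of the model also gives up precision.

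**Working it through.** **Inputs from the article.** Total size: "The MIMeRiC trial is an RCT with 2 parallel groups (N=418) and 12 months follow-up". The allocation ratio is not given (patients are "randomized to usual care (control) or usual care plus a follow-up program with medication review and MI"), so I assume 1:1, or 209 per arm. The negative-attitude share f is 10/21 = 0.476 from the pilot. The article gives no power figure for the beliefs analysis, so there is none to reproduce.

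**Assumptions (none is in the article).** The four categories are collapsed to accepting or not at 15 months. Among negative-attitude patients, 30% of controls and 50% of intervention patients are accepting. Among baseline-accepting patients, 80% remain so in both arms. There is no loss to follow-up, and the test is two-sided at 5%.

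**Formula.** Power = Φ(difference/SE − 1.96), with SE = √[p0(1−p0)/n + p1(1−p1)/n].

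**All patients.** Control: 0.476×0.30 + 0.524×0.80 = 0.562. Intervention: 0.476×0.50 + 0.524×0.80 = 0.657. The difference is 0.095, that is f × 0.20. SE = 0.0475 and power = Φ(2.005 − 1.96) = 52%.

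**Negative-attitude stratum.** n = 209×0.476 = 99.5 per arm, difference 0.20, SE = 0.0680, power = Φ(2.942 − 1.96) = 84%. (With the pooled-variance formula the two figures are 51% and 83%.)

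**All patients, analysed by baseline category.** SE = √[0.476²×0.46/99.5 + 0.524²×0.32/109.5] = 0.0430. Here 0.46 is 2 × the mean variance at 30% and 50% (0.21 + 0.25), and 0.32 is 0.16 + 0.16. Power = Φ(2.214 − 1.96) = 60%.

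**Arm-by-attitude interaction.** Difference of differences 0.20, SE = √[0.46/99.5 + 0.32/109.5] = 0.0869, power = Φ(2.303 − 1.96) = 63%.

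**Sensitivity to the share and the effect** (accepting patients 80% in both arms):

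| Share | Effect in stratum | Power, all patients | Power, stratum |
|---|---|---|---|
| 0.30 | 20 points | 26% | 65% |
| 10/21 | 15 points | 32% | 60% |
| 10/21 | 20 points | 52% | 84% |
| 10/21 | 25 points | 72% | 96% |
| 0.60 | 20 points | 70% | 91% |

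The pilot share is imprecise: the exact 95% interval for 10/21 is about 26% to 70%. With about 15% loss (178 per arm), the base case falls to 46% and 77%.

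**Sensitivity to benefit in accepting patients** (share 10/21, stratum effect 20 points, stratum power 84% throughout):

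| Accepting patients, control vs intervention | Pooled difference | Power, all patients | Power, interaction |
|---|---|---|---|
| 80% vs 80% | 9.5 points | 52% | 63% |
| 80% vs 84% | 11.6 points | 69% | 46% |
| 80% vs 88% | 13.7 points | 84% | 30% |
| 80% vs 90% | 14.8 points | 89% | 22% |

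The second table matters most. The power gap depends on little or no effect in accepting patients. At an 8-point benefit it is gone, and at 10 points the all-patient test is the stronger one.

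**The case against.** The strongest reply is that the all-patient comparison is the right overall estimate. After the pilot the team chose to treat everyone whatever their attitude. The section on patients' adherence behaviour says concerns tend to grow after a coronary event. Methods for Research Question 3 says the groups have no sharp boundary and that adherence problems can also arise in accepting patients. Category proportions at 15 months capture prevented decline as well as improvement. This stands, and it is why the all-patient comparison should stay primary.

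Three stronger readings are tempting and should be resisted:

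- A reader might infer that about half the sample has nothing to change. The Conceptual Model of Change does say "The intervention can only affect the outcomes if a patient has a problem with adherence", but the sentence goes on to cover problems expected in future and problems of treatment quality, and it concerns the trial outcomes rather than beliefs. The Research Question 4 wording is primarily, not only.
- A reader might infer that the strata were created for a subgroup analysis. The article presents them only as a randomisation factor.
- A reader might take 52% against 84% as the trial's actual loss. It is one scenario built on assumed rates.

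It can also be said that the article already covers the point or leaves it to a fuller document. Item 2 is descriptive and by arm, item 5 has no control group, and the additional analyses allowed under Integrating Results of Analysis are for hypotheses that arise once trial outcomes are combined with process data. None is a prespecified randomised comparison by baseline attitude. A fuller plan may add one, but this article fixes the analyses, their ranking and the covariates, and offers itself as the prespecification.

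Two further objections stand and shape the remedy. The interaction test is weak. And the article does not say which of the four categories count as negative.

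**Conclusion.** The point holds in a limited form. The listed beliefs analyses do not estimate the effect where the article says belief change is mainly intended, and they omit the stratification factor from the model. This is a gap between stated mechanism and stated analysis; it does not make the primary comparison invalid.

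If the effect is confined to negative-attitude patients, the pooled difference is f times the effect in that group: about 0.48 of it at the pilot share, so 20 points becomes 9.5, with power of about 52% rather than 84%. That rests on the assumed rates, 1:1 allocation, no loss, a share from 21 pilot patients and, above all, no effect in accepting patients. The documents do not settle that last assumption. Estimates by baseline attitude are useful under either possibility, because they would show which one applies.

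**What to change.** Keep the all-patient comparison at 15 months as primary and make two changes:

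1. Add baseline belief category, the randomisation stratification factor, to the covariates. In the base case this raises power from about 52% to 60%.
2. Add a prespecified secondary mechanism analysis: the between-arm difference at 15 months, with its confidence interval, within each baseline attitude group. State in advance which of the four categories count as negative.

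Report the arm-by-attitude interaction as supportive only. For a 20-point effect its power is about 63% at best, when accepting patients gain nothing, and about 30% if they gain 8 points, so a non-significant interaction should not be read as equal effects.

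No new data are needed. The cost is one more secondary analysis with limited precision: in the base case the stratum difference has a 95% interval of about ±13 points (1.96×0.0680), against about ±9 for all patients (1.96×0.0475).
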